## Abstract

**Background:**

Anxiety disorders are one of the most common psychological problems in adolescents. The school system has been identified as an ideal setting for the implementation of prevention and early intervention programs for anxiety; however, few programs are routinely delivered in schools and little is known about the best delivery methods. The aim of the current project is two-fold: to test the effectiveness of an intervention program for anxiety relative to a control condition, and to compare two methods of implementing the program.

**Methods/design:**

This study is a three-arm cluster randomised controlled trial consisting of a wait-list control condition and two intervention conditions evaluating the effectiveness of an Internet-based program for preventing generalised anxiety. The first intervention condition will involve classroom teachers supervising student completion of the intervention program, while the second intervention condition will involve the classroom teacher and an education officer from the local youth mental health centre supervising the program’s completion. At least 30 schools from across Australia will be recruited to the trial, with adolescents aged between 14 and 18 years invited to participate. Participants in the intervention conditions will complete the e-couch Anxiety and Worry program during class periods over six weeks. The primary outcome measure will be a scale reflecting the number and severity of generalised anxiety symptoms, while secondary outcomes will be symptoms of depression, social anxiety and anxiety sensitivity. Data will be collected at pre-intervention, post-intervention, 6- and 12-month follow-up. Intention-to-treat analyses will be conducted.

**Discussion:**

If demonstrated effective, a new service delivery model for the implementation of mental health programs in schools could be indicated. Such a model would significantly contribute to the mental health of young people in Australia by providing preventive interventions for mental health problems and consequently reducing the need for clinical services.

**Trial registration:**

The Australian New Zealand Clinical Trials Registry ACTRN12610001103055

## Background

Anxiety disorders are one of the most common psychological problems in adolescents and young adults and often precedes the development of depression [1,2]. The 1-year prevalence rate of anxiety disorders in this population is estimated to lie between 5% and 21% [3-6], with 8% to 27% of young people experiencing an anxiety disorder during adolescence [3-5,7]. The effect of anxiety disorders on the wellbeing of young people is substantial, with their social, emotional and academic functioning often severely affected [8]. If left untreated, the effects of anxiety typically continue into adulthood where further occupational, economic and interpersonal difficulties can arise [9].

Given the high prevalence rate of anxiety disorders and their associated negative effects, efforts directed at prevention and early intervention should be paramount. Preventing the onset or worsening of anxiety symptoms during adolescence would not only reduce and prevent the short- and long-term effects described above, but could also contribute to reducing the need, and thus cost, of clinical treatment [10], and potentially prevent the onset of depressive disorders [11].

The school system has been identified as an ideal setting for the implementation of prevention and early intervention programs for anxiety, due to its unparalleled contact with youth [12,13]. The delivery of anxiety intervention programs in schools is also important given the low rates of disorder identification [14,15] and help-seeking behaviour by adolescents [16,17]. Many young people, particularly men, do not seek help for anxiety. This was reflected in the 2007 National Survey of Mental Health and Wellbeing which found that only 13.2% of young men aged between 16 and 24 years with a mental disorder had sought help [18].

A number of effective school-based prevention and early intervention programs for anxiety have been developed and implemented [19,20]. These programs tend to target current anxiety levels with the aim of preventing anxiety symptoms from worsening or preventing the development of anxiety symptoms at all. Despite their effectiveness, these programs are not routinely delivered in schools. The reasons for the lack of uptake of effective programs are not clear. It is apparent however, that teachers are often not keen to deliver mental health programs in the classroom due to a lack of training or general expertise in the field [21]. Teachers may be anxious about the effect of mental health materials on their students, and may be concerned that they themselves will be unable to handle any consequences. These problems indicate an important need to develop appropriate methods of delivering and implementing effective anxiety intervention programs in schools, particularly if schools are to function as a vector for mental health symptom reduction and prevention. A major concern has also been in the perception that behavioural change needs to be maintained, and that appropriate channels to seek help when required are needed in a comprehensive model.

The aims of the present project, therefore, are two-fold. The first is to test the effectiveness of an online intervention program for anxiety relative to a control condition. The second is to determine whether an enhanced version of the program which incorporates access to a potential service provider results in improved outcomes relative to the standard teacher administered intervention. The anxiety intervention to be evaluated in the current trial is an automated anxiety literacy and cognitive behavioural therapy (CBT) program delivered via the Internet. This program has the potential to overcome some of the problems associated with traditional face-to-face school-based programs by providing a self-directed program to students that requires little teacher training or knowledge. The automated delivery of Internet-based interventions also ensures the fidelity of a program, while its self-directed nature can promote independent learning.

The use of online programs in schools for the prevention of depression has been found to be effective in the trials to date [22-24]. The YouthMood Project [24], which evaluated the MoodGYM program in 30 schools from across Australia in a universal prevention trial, found significant reductions in depressive symptoms in men (Cohen’s *d* = 0.27-0.43), and in anxiety symptoms in men and women (*d* = 0.15-0.25). Earlier controlled trials of the MoodGYM program in schools found similar effects [22,23].

Two delivery methods will be compared to the control condition, in which students will continue their usual classes during the intervention phase of the trial. The first implementation method to be tested in the current trial will involve classroom teachers supervising student completion of the Internet-based program for reducing and preventing anxiety in schools (‘e-GAD school method’ condition). The second implementation method adds the support and assistance of *headspace* to the first approach (‘e-GAD health service method’ condition). *headspace* is an Australian youth mental health foundation which provides mental health services and support for young people aged 12 to 24 years. *headspace* will guide students in the completion of the program and provide support to students if and when they disclose personal difficulties, or require further help and support. *headspace* will also promote the mental health services that they provide and raise student awareness of the help-seeking options available. This condition will ascertain whether *headspace* assisted delivery differs in effectiveness from that of the teacher delivered intervention.

### Aims of the project

#### Primary aim

(1) To evaluate the efficacy of the e-couch Anxiety and Worry program in reducing and preventing symptoms of anxiety in an adolescent school-based population relative to usual school classes (wait-list control). Both the teacher delivered and *headspace* assisted conditions will be compared to the wait-list control condition.

#### Secondary aims

(1) To compare classroom delivered e-couch with *headspace* assisted e-couch to determine whether the addition of *headspace* contact in the classroom improves outcomes.

(2) To evaluate the effect of the e-couch Anxiety and Worry program (teacher delivered or *headspace* assisted) on depressive symptoms, wellbeing, anxiety literacy, anxiety stigma, and help-seeking attitudes, intentions and behaviour compared to the wait-list control condition.

(3) To assess participant satisfaction, attendance and adherence to the e-couch Anxiety and Worry program, and to determine the predictors of these outcomes, and their relationship to mental health outcomes.

(4) To evaluate the effect of the e-couch Anxiety and Worry program on individuals with and without clinical levels of anxiety or depressive symptoms at pre-intervention.

#### Hypotheses

(1) The e-couch Anxiety and Worry program (whether delivered by the school or the health service method) will be associated with significantly lower levels of generalised anxiety symptoms at post-intervention, 6- and 12-month follow-up, than the wait-list control condition.

(2) The effect of the e-couch Anxiety and Worry program on anxiety symptoms and help-seeking behaviour will be greater in the guided e-GAD health service method than in the e-GAD school method.

(3) The e-couch Anxiety and Worry program (delivered by either method) will be associated with significantly lower levels of depressive symptoms and anxiety stigma, and higher levels of wellbeing, anxiety literacy and help-seeking attitudes, intentions and behaviours at post-intervention, 6- and 12-month follow-up, than participants in the wait-list control condition.

(4) The e-couch Anxiety and Worry program (delivered by either method) will prevent the development of anxiety and depressive symptoms over 12 months in those who are asymptomatic at baseline.

## Methods

### Study design

This study will be implemented as a three-arm cluster stratified randomised controlled trial (RCT) with two interventions conditions (e-GAD school method condition and e-GAD health service method condition) and a wait-list control condition. There will be four measurement occasions: pre-intervention, post-intervention, 6- and 12-month follow-up. This study was granted ethical approval by the Australian National University Human Ethics Committee (protocol number 2010/550) and the individual Sate and Territory Education Departments responsible for each participating school.

### Recruitment

At least 30 schools from across Australia will be recruited to participate in the trial. Schools will be drawn from rural and metropolitan areas and male and female adolescents in grades 9 to 12 (aged 14 to 18 years) will be invited to participate. Schools will be recruited according to the location of participating *headspace* centres. Information letters will be sent to each school informing them of the project. A briefing day will be held for all participating schools prior to the trial’s implementation. The briefing day will provide schools with an opportunity to meet other schools involved in the trial and to receive detailed information and instruction on the delivery of the trial. Information and consent forms will be distributed to all invited participants and their parents/guardians, with written informed consent required from both.

### Randomisation

Each participating school (cluster) will be randomised to one of the three conditions. Randomisation will occur according to *headspace* centre location. Cluster randomisation will be employed for administrative convenience, to avoid wait-list control condition contamination, and for the ecological validity of providing the intervention at the cluster level [25,26]. A statistician not involved in the implementation of the trial will randomly allocate schools within each *headspace* centre to the intervention or wait-list control conditions using a computerised random number generator. The identity of schools will be concealed from the statistician during this process.

### Procedure

All participating students will be invited to complete a pre-intervention, post-intervention, 6- and 12-month follow-up questionnaire. Participants randomised to the intervention conditions will undertake the e-couch Anxiety and Worry program (http://www.ecouch.anu.edu.au) during one class period a week (30 to 40 min) for 6 weeks following the pre-intervention questionnaire. All participating students will be provided with an e-couch Anxiety and Worry program login and password, which will be linked to their questionnaire ID. This will allow program adherence and completion rates (which are recorded automatically by the e-couch Anxiety and Worry program) to be linked to anxiety and other variable outcomes. Individual sections of the e-couch Anxiety and Worry program will be made available to participants each week to prevent participants completing the program prematurely. The e-couch Anxiety and Worry program will be incorporated into the school curriculum and will be delivered in a range of subject areas, including pastoral care, health, personal development and English.

Classroom teachers in the e-GAD school method condition will supervise students’ completion of the e-couch Anxiety and Worry program, with no direct teaching. Participants exhibiting elevated levels of anxiety and/or depression will be referred to the school counsellor in accordance with usual school procedures. School counsellors will be provided with clear referral pathways to the local *headspace* centre if further support is required.

Classroom teachers in the e-GAD health service method condition will supervise students’ completion of the e-couch Anxiety and Worry program, with the assistance and support of *headspace* centre staff. h*eadspace* centre staff will provide a brief description of the *headspace* service, and the contact details of the local *headspace* centre. In the classroom they will respond to student questions about the program and offer referral pathways for students who request help. The *headspace* centre staff will also act as an external source of contact for students who may not feel comfortable approaching school staff for assistance. Essentially the *headspace* centre staff will guide students in completion of the program and promote the importance of help-seeking behaviour for mental health problems.

Schools in the wait-list control condition will continue their usual classes during the intervention phase of the trial. The activities undertaken by participants in the wait-list control condition will be dependent on the class in which the trial is implemented. Participants in the wait-list control condition schools will be offered the e-couch Anxiety and Worry program at the conclusion of the trial (following the 12-month follow-up questionnaire). All classroom teachers will be provided with a step-by-step guide to assist them in the administration of the trial questionnaires and the delivery of the e-couch Anxiety and Worry program.

### Intervention

The e-couch Anxiety and Worry program (http://www.ecouch.anu.edu.au) consists of two major parts: psychoeducation and a series of evidence-based toolkits for anxiety consisting of CBT, relaxation and physical activity. The psychoeducation section is modelled on mental health literacy interventions previously found to improve attitudes and reduce symptoms for depression and anxiety [27,28]. The content of the psychoeducation section is as follows: definition of worry; distinction from stress; differentiation of worry, fear and anxiety; description of anxious thinking; differentiation of GAD from panic disorder (PD), specific phobia and social anxiety disorder (SAD), adjustment disorder and post-traumatic stress disorder (PTSD); description of risk factors for GAD; the problem of co-morbidity; consequences of anxiety; and treatments for anxiety including medical, psychological and lifestyle treatments. The content of these sections is based on reviews of evidence of alternative and lifestyle treatments [29] and on clinical practice guideline [28].

The CBT toolkit for anxiety is based on previously developed material with confirmed efficacy for anxiety cognitions and beliefs in at-risk individuals [30,31]. This toolkit teaches participants about worry, what causes and compounds worry, how to detect and reduce worry, how to problem solve the issues causing worry, how to change thoughts to prevent and reduce worry, and exploring the feelings behind worry. This toolkit essentially focuses on the cognitive aspects of worry and how to change them. The vast majority of school-based prevention programs for anxiety are based on CBT techniques such as these and have been found to be both efficacious and safe [19,20].

The relaxation toolkit contains a mindfulness meditation exercise and progressive muscular relaxation exercise. In the mindfulness meditation exercise participants are encouraged to focus on their breathing and to be in the present moment, rather than lost in thoughts, memories or the future. Mindfulness meditation promotes a sense of calm. Progressive muscular relaxation involves tensing and relaxing the different muscle groups in the body. This exercise helps participants to recognise the tension in their bodies and how to relieve it.

The physical activity toolkit was designed to help participants evaluate their own level of physical activity, learn some strategies for increasing or maintaining their physical activity level, and teach them some of the benefits of being physically active. The toolkit recommends 30 min of physical activity a day, which includes partaking in day-to-day activities such as hanging out the washing, gardening and walking up stairs. The toolkit does not focus on strenuous physical activity and participants who are not currently physically active are advised to start slowly.

### Assessments

Table 1 presents the scales that will be administered at each measurement occasion in the Y-Worri Trial.

**Table 1 T1:** Questionnaire scales for the Y-Worri trial

	**Pre-intervention**	**Post-intervention**	**6-month follow-up**	**12-month follow-up**
Demographics	X			
Anxiety history	X			
Self-perceived emotional health	X	X	X	X
SCAS	X	X	X	X
GAD-7	X	X	X	X
SAS-A	X	X	X	X
CASI	X	X	X	X
CES-D	X	X	X	X
WEMWBS	X	X	X	X
GASS (Personal)	X	X	X	X
GASS (Perceived)	X			
Predictors adherence	X	X	X	X
Mental health literacy	X	X	X	X
Anxiety literacy (A-Lit)	X	X	X	X
Days out of role	X	X	X	X
ATSPPH-SF	X	X	X	X
Adapted GHSQ	X	X	X	X
Adapted AHSQ	X	X	X	X
Usefulness of e-couch		X	X	X
Use of e-couch strategies		X	X	X
Helpfulness of e-couch strategies		X	X	X

AHSQ, Actual Help-Seeking Questionnaire; ATSPPH-SF, Attitudes Toward Seeking Professional Psychological Help- Short Form; CASI, Childhood Anxiety Sensitivity Index; CES-D, Center for Epidemiological Studies Depression Scale; GASS, Generalised Anxiety Stigma Scale; GHSQ, General Help-Seeking Questionnaire; SAS-A, Social Anxiety Scale for Adolescents; SCAS, Spence Children’s Anxiety Scale; WEMWBS, The Warwick-Edinburgh Mental Well-being Scale.

#### Demographic variables

The following demographic variables will be measured: age, sex, grade, rural location, first language, Aboriginal or Torres Strait Islander origin, living situation, and participant history of anxiety and help-seeking behaviour.

#### Generalised anxiety disorder

Generalised anxiety disorder (GAD) symptoms will be the primary outcome of interest for the study and will be measured on the Spence Children’s Anxiety Scale (SCAS) [32] and the GAD-7 [33]. An effect size of approximately 0.3 is expected at both post-intervention and follow-up. The expected 0.3 effect size is further discussed in the power calculations. The SCAS is a 44-item self report questionnaire composed of 38 items that assess specific anxiety symptoms relating to six subscales, namely generalised anxiety, social phobia, separation anxiety, panic attack/agoraphobia, obsessive-compulsive disorder and physical injury fears, and six positive ‘filler items’ designed to reduce negative response bias. Each item is responded to on a four point scale ranging from 0 (never) to 3 (always). A total scale score is calculated by summing the scores for the 38 anxiety symptom items. The total scale score on the SCAS ranges from 0 to 114, with higher scores reflecting greater levels of anxiety. The GAD-7 is a brief seven-item self-report scale that measures generalised anxiety symptoms. Each item is responded to on a four-point scale ranging from 0 (not at all) to 3 (nearly every day). A total scale score is calculated by summing item scores, with total scale scores ranging from 0 to 21. Higher GAD-7 scores indicate greater levels of generalised anxiety symptoms. An additional eighth item will also be included to assess the impact of anxiety symptoms, if present, on functioning.

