### Statistical analysis

Primary analyses of the outcomes will be undertaken on an intent-to-treat basis, including all participants randomised regardless of treatment actually received or withdrawal from the study. Mixed models repeated measures (MMRM) analyses will be used because of the ability of this approach to include participants with missing data. This approach will also allow potential clustering effects (students within the same school being more alike) to be explored and accounted for within the analyses. If required appropriate transformations of scores will be undertaken. Should outliers or distributional problems prelude standard methods, generalized mixed models will be applied. A series of analyses will be conducted to assess the effectiveness of the e-couch Anxiety and Worry program in preventing and reducing symptoms of generalised anxiety. These analyses will include a general analysis of intervention effects comparing the two delivery method conditions to the wait-list control condition, as well as separate analyses to test the effectiveness of the individual delivery methods. MMRM analyses of the secondary variables (for example, depressive symptoms, anxiety stigma) will also be conducted.

Subsample analyses will also be conducted with participants who scored above and below the clinical cutoff scores for anxiety and depressive symptoms at pre-intervention. The preventive subsample analyses will be conducted to identify the true preventive effects of the intervention, while the clinical subsample analyses will be undertaken to provide valuable information regarding the utility of the e-couch Anxiety and Worry program as an indicated intervention. MMRM ANOVAs, identical to those applied to the full sample, will be conducted on the four subsamples of participants. In addition to this, analyses will be conducted to identify any significant differences in the proportion of participants in the intervention and wait-list control conditions who meet criteria for clinical caseness at post-intervention, 6- and 12-month follow-up in the preventative sub-sample analyses, or remain clinical cases in the clinical subsample analyses (attributable risk reduction). The number needed to treat (NNT) will be calculated with 95% confidence intervals (CIs).

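### The abstract promises one primary scale, but the Methods use two (SCAS and GAD-7) with no ranking and no rule for combining them

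*Protocol article*

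**What the plan says.** The abstract (Methods/design) uses the singular and names no instrument: "The primary outcome measure will be a scale reflecting the number and severity of generalised anxiety symptoms".

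Under Assessments, the subsection on generalised anxiety disorder makes generalised anxiety symptoms the primary outcome and says that they "will be measured on the Spence Children’s Anxiety Scale (SCAS) [32] and the GAD-7 [33". For the SCAS, the only score defined is a total: "A total scale score is calculated by summing the scores for the 38 anxiety symptom items". Those items span generalised anxiety, social phobia, separation anxiety, panic/agoraphobia, obsessive-compulsive symptoms and physical injury fears. A generalised anxiety subscale is listed as a component, but no score for it is described. The GAD-7 total (0 to 21) measures generalised anxiety alone.

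Hypothesis 1 predicts "significantly lower levels of generalised anxiety symptoms at post-intervention, 6- and 12-month follow-up, than the wait-list control condition". The Statistical analysis section plans "a general analysis of intervention effects comparing the two delivery method conditions to the wait-list control condition". To this pooled comparison it adds one for each active arm on its own: "as well as separate analyses to test the effectiveness of the individual delivery methods". An alpha of .05, two-tailed, appears once, in the power calculation, which does not say which scale, occasion or contrast it refers to.

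**The concern.** The primary measure determines which result answers the primary aim. Here one part of the article says there is one such measure and another part gives two. If the SCAS total and the GAD-7 disagree, the text does not say whether the program worked. Disagreement is quite possible, because most SCAS subscales concern something other than generalised anxiety, and the abstract lists social anxiety as a secondary outcome although social phobia items count in the SCAS total.

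Two things are at stake. If a positive result on either scale counts, the error rate of the primary claim exceeds 5%. If both must succeed, or alpha is split, the power is below the figure stated. The gap also carries over to the subsample and caseness analyses, which use a clinical cutoff for anxiety without naming the scale it belongs to.

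**Working it through.** **Inputs from the article.** 525 students with data; ICC 0.02; class size 25; design effect 1.48; effective sample size 354; effect 0.3 SD; correlation over time 0.5; two-sided alpha .05; power 80%; three arms; three post-baseline occasions.

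**Assumptions, not in the article.** Equal allocation, so 354/3 = 118 effective students per arm. Correlation between SCAS and GAD-7 of 0.5 to 0.8.

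**1. Reproducing the stated power**
- Design effect: 1 + (25 − 1) × 0.02 = 1.48. Effective size: 525/1.48 = 354.7, against 354 stated.
- Mean of three occasions with correlation 0.5: variance factor (1 + 2 × 0.5)/3 = 0.667.
- Pairwise contrast: 0.3/√(0.667 × 2/118) = 2.822. Power = Φ(2.822 − 1.960) = 80.6%, which matches.
- Splitting 354 into two groups of 177 with a single measurement also matches: 0.3/√(2/177) = 2.822, again 80.6%.
- A single-occasion pairwise contrast does not match: 0.3/√(2/118) = 2.304, power 63.5%. With baseline adjustment (variance factor 1 − 0.5² = 0.75) it is 75.8%.

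Both matching routes are one test on one scale at an unadjusted .05.

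**2. Either scale counts, each at .05 (one contrast, one occasion)**

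Error = 1 − P(|Z₁| < 1.96 and |Z₂| < 1.96), with Z₁ and Z₂ bivariate normal.

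| Scale correlation | At least one p < .05 | In the program's favour |
|---|---|---|
| 0.5 | 9.1% | 4.5% |
| 0.7 | 8.3% | 4.2% |
| 0.8 | 7.8% | 3.9% |

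The single-scale figures are 5% and 2.5%.

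**3. Alpha split over two scales (.025 each)**
- Pairwise, averaged over occasions: Φ(2.822 − 2.241) = 71.9%.
- Regaining 80% needs 141 effective students per arm: 3 × 141 × 1.48 = 626 students, against 525.
- Pooled contrast (236 against 118): 0.3/√(0.667 × (1/118 + 1/236)) = 3.259. Power is 90.3% at .05 and 84.6% at .025.

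**4. Both scales must succeed, each at .05**
- The error rate does not exceed 5%.
- With a 0.3 SD effect on both scales, pairwise joint power is P(Z₁ < 0.862 and Z₂ < 0.862): 69.5% at correlation 0.5 and 73.6% at 0.8.

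**5. Worst case, for scale only**
- 2 scales × 3 occasions × 3 contrasts (pooled, and each method against wait-list) = 18 tests.
- Simulated under no effect (200,000 draws, scale correlation 0.5–0.8, occasion correlation 0.5–0.6), at least one p < .05 occurs in about 32–38% of trials, and one in the program's favour in about 16–20%.
- The independence bound, 1 − 0.95¹⁸ = 60.3%, is not realistic because the tests are correlated.

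**The case against.** A reader might infer that the plan makes 18 unordered primary tests at .05, any one of which could be claimed as success. The article does not support that reading:
- The Statistical analysis section specifies mixed models for repeated measures and does not say that each occasion is tested separately. An overall group or group-by-time test fits the wording as well.
- Hypothesis 1 can be read as requiring a difference at all three occasions, in which case the occasions add no inflation. The article does not state that rule either.
- Alpha .05 is a power-calculation input, not a stated decision rule.
- One route that reproduces 80% averages the occasions, which would remove the factor of three. The two-groups route fits equally well, so this is not settled.
- There is some structure: comparison with wait-list is the primary aim, comparison of the two delivery methods is secondary, and the general analysis is listed before the separate ones.
- A testing order or adjustment is normal content for a statistical analysis plan. None is shown here, so its absence from the article is no finding.

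All of this stands against the 18-test count. None of it removes the conflict between one scale and two, which lies in the article's own text.

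**Conclusion.** The point holds as a contradiction over the primary measure. The abstract has one unnamed scale; the Methods have two instruments of different scope, with no ranking and no both-or-either rule.

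The documented size is modest but real: about 8–9% instead of 5% for one contrast at one occasion if either scale counts, or a pairwise power of about 72% instead of about 80% if alpha is split. The error rate rests on the assumed scale correlation; the power figures rest on equal allocation and on averaging over occasions. The 32–38% figure is a worst case under a permissive reading and should not be reported as the plan's error rate.

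The matter should be settled before analysis. The Trial status section reports data collection as ongoing, and a primary scale chosen after results by arm are known would not be credible.

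**What to change.** Before any outcome data are examined by arm:

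1. Name one primary scale and make the other secondary. The GAD-7 total is the natural candidate, as the only scored measure described that covers generalised anxiety alone. If the sponsor prefers the SCAS, state whether the total or the generalised anxiety subscale is meant. Alternatively, keep both under an explicit rule that both must succeed.
2. State which contrast with wait-list, and which occasion or overall test, decides hypothesis 1.
3. Align the abstract with the generalised anxiety disorder subsection, and say which scale the anxiety cutoff in the subsample analyses refers to.

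The cost is wording. With one named scale, results on the demoted scale lose confirmatory status, but there is no need to split alpha between scales. With the both-must-succeed rule, the cost is power: roughly 70–74% pairwise under the assumptions above.
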